## Abstract

**Background:**

Imaging has become a routine part of heart failure (HF) investigation. Echocardiography is a first-line test in HF given its availability and it provides valuable diagnostic and prognostic information. Cardiac magnetic resonance (CMR) is an emerging clinical tool in the management of patients with non-ischemic heart failure. Current ACC/AHA/CCS/ESC guidelines advocate its role in the detection of a variety of cardiomyopathies but there is a paucity of high quality evidence to support these recommendations.

The primary objective of this study is to compare the diagnostic yield of routine cardiac magnetic resonance versus standard care (that is, echocardiography with only selective use of CMR) in patients with non-ischemic heart failure. The primary hypothesisis that the routine use of CMR will lead to a more specific diagnostic characterization of the underlying etiology of non-ischemic heart failure. This will lead to a reduction in the non-specific diagnoses of idiopathic dilated cardiomyopathy and HF with preserved ejection fraction.

**Design:**

Tertiary care sites in Canada and Finland, with dedicated HF and CMR programs, will randomize consecutive patients with new or deteriorating HF to routine CMR or selective CMR. All patients will undergo a standard clinical echocardiogram and the interpreter will assign the most likely HF etiology. Those undergoing CMR will also have a standard examination and will be assigned a HF etiology based upon the findings. The treating physician’s impression about non-ischemic HF etiology will be collected following all baseline testing (including echo ± CMR). Patients will be followed annually for 4 years to ascertain clinical outcomes, quality of life and cost. The expected outcome is that the routine CMR arm will have a significantly higher rate of infiltrative, inflammatory, hypertrophic, ischemic and ‘other’ cardiomyopathy than the selective CMR group.

**Discussion:**

This study will be the first multicenter randomized, controlled trial evaluating the role of CMR in non-ischemic HF. Non-ischemic HF patients will be randomized to routine CMR in order to determine whether there are any gains over management strategies employing selective CMR utilization. The insight gained from this study should improve appropriate CMR use in HF.

**Trial registration:**

NCT01281384.

## Background

Innovations in imaging create the potential for earlier, less invasive and more accurate diagnoses of disease and may ultimately improve health outcomes. However, imaging is also one of the fastest growing health care expenditures. The 2005, the US Medicare Payment Advisory Committee found that the growth of cardiac imaging was nearly double any other cardiac procedure [1]. This underscores the need to ensure efficient development, implementation and use of this health care resource in order to provide value to patients and society. However an evaluation of the clinical and economic impact of cardiac imaging has lagged behind the pace of the technology. A recent review of current ACC/AHA guidelines found that only 11% of recommendations provide level of evidence A (multiple randomized controlled trials and meta analyses) and 48% have level of evidence C (consensus opinion) [2]. In cardiac diagnostics, level of evidence A is found in only 2%, level of evidence C in 17% and in 44% of recommendations there is no evidence provided. These observations underscore the need for more evidence based trials, particularly in cardiac imaging.

In 2007, the Canadian Institutes of Health Research New Frontiers Program consensus conference identified the urgent need for improved evaluation of imaging in relation to outcomes and translation from bench to bedside, particularly in heart failure (HF). In response, we established IMAGE-HF, a synergistic multi-disciplinary, multi-modality, multi-center Canada-Finland team comprised of seven Canadian sites and three Finnish sites. The main goal of IMAGE-HF is to evaluate cardiac imaging using existing clinical practice strategies for HF and their links to relevant outcomes (level 1 projects) and to create a unique translational platform for the evaluation of novel imaging biomarkers in animal models of HF and in HF patient populations (level 2 and 3 projects). IMAGE-HF 1-B, rOUTine versus Selective MAgnetic Resonance in non-ischemic HearT Failure-HF (OUTSMART-HF), will study the role of cardiac magnetic resonance (CMR) in non-ischemic heart failure.

### Statement of the problem

Population studies reveal that 50% of HF patients have preserved ejection fraction (HFPEF) and a dismal prognosis similar to those HF patients with reduced ejection fraction (HFREF) [3-5]. Among the HFREF patients, 50% have no significant underlying coronary artery disease [6]. The most common identifiable causes for non-ischemic HF include hypertension, valvular heart disease, arrhythmia, post-viral and acquired or inherited cardiomyopathies. However, standard measures of cardiac morphology and function obtained on imaging testing provide only limited information about HF etiology or prognosis [7] and, other than ejection fraction (EF), have a limited role in therapeutic decision-making.

Echocardiography is well suited for the assessment of HF patients because it is widely available and provides reliable information on cardiac performance in normal and diseased states. It is also considered the best imaging modality for valvular disease, a significant finding in 35% of patients hospitalized with HF [8]. More recent technological advances such as tissue velocity and strain have shed new insights into pathophysiological mechanisms that may be particularly pertinent in HFPEF [9-11]. Furthermore, diastolic dysfunction determined by Doppler echocardiography is common in HF patients and has been shown to be a predictor of increased mortality during longitudinal follow-up [12]. Data from the Rochester Epidemiologic Program revealed that there was a lower risk of death in HF patients who had undergone echocardiograms compared to those who had not, suggesting that echocardiography improved care and should be part of the routine investigation of HF patients [13]. Given the available evidence and its extensive clinical experience, echocardiography is recommended as a class 1 indication in the initial investigation of all HF patients [14-16].

CMR is emerging as a valuable tool in the diagnosis of non-ischemic heart failure and is considered preferable or at least equivalent to other diagnostic tests in several cardiomyopathies [17]. Ventricular volumes and function derived from CMR is more accurate than standard echocardiography due to high inter-test and inter-observer reproducibility [18]. Moreover, CMR offers insight into myocardial tissue characteristics [19], with specific regional patterns of myocardial injury [20]. Non-infarct and infarct patterns have been reported in 28% and 13%, respectively, of patients with HF and unobstructed coronary arteries [19]. In a recent single site study of 120 patients with new onset HF, CMR had a 97% accuracy for differentiating an ischemic from a non-ischemic etiology [21]. CMR has been used to characterize myocarditis [22-24], sarcoidosis [25], hypertrophic cardiomyopathy [26], hemochromatosis [27] and amyloidosis [28]. CMR thus offers a new class of diagnostic and prognostic parameters for personalized therapy and prevention of HF. However, there is a need to understand how such data impacts diagnosis, clinical decision-making and patient outcomes.

The diagnosis of HFPEF remains challenging as discussed in negative drug trials to date [29-31]. Diagnostic criteria incorporating clinical signs and symptoms, biomarkers, imaging and/or hemodynamic parameters have been proposed but not studied well [32]. Diffuse myocardial fibrosis as assessed by CMR has been utilized as a novel diagnostic target in HF [33] and cardiomyopathy subjects [34]. Patients with HFPEF are known to have increased myocardial collagen and fibrosis and hence CMR could be used to study this group.

Despite growing evidence of the utility for CMR in various cardiomyopathies, a comprehensive study examining its role in HF is lacking.

### Objectives

#### Primary objective

To compare the diagnostic yield of routine cardiac magnetic resonance versus standard care (that is, echocardiography with only selective use of CMR) in patients with non-ischemic heart failure. The diagnostic categories of HF to be considered in this study include: idiopathic dilated cardiomyopathy, infiltrative cardiomyopathy, inflammatory cardiomyopathy, hypertrophic cardiomyopathy, heart failure with preserved ejection fraction (HFPEF), ischemic cardiomyopathy, mixed etiology and ‘other’ (for example, pericardial disease, adult congenital heart disease, arrhythmogenic right ventricular cardiomyopathy).

#### Secondary objectives

To determine the effects that routine use of CMR in non-ischemic HF has on therapeutic decisions on the Composite Clinical Endpoint (CCE), cardiac function, symptoms, quality of life (QoL), and costs. Ancillary measurements will include the safety of imaging tests and adverse reactions to gadolinium contrast agent.

### Hypotheses

#### Primary hypothesis

Routine use of CMR (versus selective use) will lead to a more specific diagnostic characterization of the underlying etiology of non-ischemic heart failure. This will lead to a reduction in the non-specific diagnoses of idiopathic dilated cardiomyopathy and HFPEF.

#### Secondary hypotheses

Routine use of CMR will have a significant impact on treatment decisions, and will (1) lead to more disease specific therapies and/or (2) cause a significant change in the number and class of HF medications, during follow-up. The routine CMR group will also have improved clinical outcomes (CCE), symptoms and QoL and decreased costs compared to the standard of care group during follow-up.

### Design

Randomized controlled trial comparing i) routine CMR to ii) echocardiography with selective CMR in patient with HF due to a non-ischemic cardiomyopathy (NICM) and/or HFPEF. Among patients enrolled in level 1 of IMAGE-HF, it is expected that 504 will have known NICM (or strongly suspected based on young age, absent risk factors and presenting history) and/or HFPEF (Figure 1).

**Figure 1 F1:**
[figure not shown]
**Flow diagram for OUTSMART-HF.** Abbreviations: HF = heart failure and CMR = cardiac magnetic resonance.

Tertiary care sites (in Canada and Finland) with dedicated HF programs will participate in the study (Additional file 1). Consecutive patients will be enrolled at sites with CMR programs (defined as a minimum 200 cases/year) and randomized to routine CMR or selective CMR. Non-ischemic HF patients from sites with smaller CMR programs will be included in a registry of patients undergoing routine HF care (that is, selective use of CMR). All sites will receive approval from local ethics committees (UOHI REB protocol # 2010422-01H) and patients will give written informed consent. Participants in the selective CMR arm may only undergo CMR when there is a suspicion or uncertainty for a diagnosis of: 1) infiltrative cardiomyopathy, 2) arrhythmogenic right ventricular cardiomyopathy, 3) adult congenital heart disease or 4) pericardial disease following standard HF care including echocardiography [35]. Other tertiary sites may be added in year two to three depending on recruitment needs and registry sites may become randomization sites if the experience and wait-time criteria are met.

### Study population

We will recruit patients with either newly diagnosed HF within the past 12 months or established HF patients with deterioration/decompensation within the past 12 months.

*Inclusion criteria:*

Patients with new or worsening HF as above *and*:

1) age > 18 years

2) working clinical diagnosis (known or highly suspected) of non-ischemic cardiomyopathy (NICM) or clinical diagnosis of HFPEF (signs or symptoms of heart failure with a LVEF ≥ 40%)

3) documented history of Class II-IV NYHA HF symptoms within the past 12 months

*Exclusion criteria:*

1) prior CMR and no major change in clinical condition

2) well-documented specific etiology (for example, known amyloidosis or hemochromatosis)

3) physician considers cause of heart failure is attributable to obstructive CAD

4) documented previous ST-segment elevation myocardial infarction (STEMI) (any territory) or non-ST-segment elevation myocardial infarction (NSTEMI) in the left anterior descending coronary artery territory

5) evidence of multi-vessel ischemia on stress imaging

6) ongoing need for advanced heart failure support (for example, inotropes or intra-aortic balloon pump)

7) severe valvular heart disease requiring surgery within the next six months

8) contraindications to CMR (for example, certain metallic implants, severe claustrophobia)

9) contraindications to gadolinium contrast agent (glomerular filtration rate < 30 ml/min/1.72 m^2^, pregnancy)

10) severe medical conditions that significantly affect the patient's outcome (for example, active malignancy)

11) inability to give informed consent

### Description of interventions (randomized and registry participants)

Baseline: demographic and clinical data will be collected from all participants on standardized case report forms. This data will be collected from the participant and the most recent, routine history and physical examination that have been completed by the treating physician. Quality of life questionnaires (Minnesota Living with Heart Failure (MLHFQ) and EuroQoL Quality of Life Scale (EQ5D)) will be administered. Patients at all sites will undergo standard HF investigations according to published Canadian guidelines [14,36,37]. Each center will have a HF lead, an echo lead and a CMR lead as well as a study co-ordinator.

#### Echocardiography

The performance and interpretation of echocardiography will be carried out according to established Canadian guidelines [38]. The echocardiography study and report must include the following measures: left ventricular (LV) size and systolic function (modified Simpson’s biplane formula), LV diastolic function (E/e’), LV mass (Teichholz formula), left atrial (LA) volume (biplane formula), valvular function (Doppler), right ventricular function, pulmonary arterial pressures (if possible) and pericardial assessment. Appendix A. The feasibility of implementing these standards and collaboration among multiple centers has been demonstrated in prospective echocardiography trials such as the ASTRONOMER study [39]. The new components such as strain and tissue velocity will be obtained and measured as described [40]. A standardized case report form will be completed by the echocardiographer. The most likely HF etiology based upon the echocardiogram will be provided to the referring physician.

#### CMR

Following all HF investigations (including echocardiography), study participants randomized to routine CMR as well as those requiring selective CMR will undergo a conventional scan. The CMR protocol must include an assessment of biventricular volumes and systolic function, LV mass, LA volume (biplane formula), global and regional myocardial edema using T2 weighted sequences, and hyperemia and regional myocardial fibrosis using contrast enhanced T1 weighted sequences. Appendix A. CMR interpreters participating in this trial should report a minimum of 100 cases/year. Local CMR interpreters at each participating center will be expected to complete a standardized clinical report form. The most likely HF etiology based upon the CMR will be provided to the referring physician. All CMR data acquisition and reporting will conform to current published guidelines [41,42].

The echo and CMR reports will be integrated with the other clinical data when used by the treating physician to make a final clinical determination on the HF etiology.

### Primary outcome measure - frequency of definitive diagnoses

Following the completion of all baseline testing (including echo ± CMR), the treating physician will assign a diagnosis on a standardized template using all available information. The HF categories include: idiopathic dilated cardiomyopathy, infiltrative cardiomyopathy, inflammatory cardiomyopathy, hypertrophic cardiomyopathy, heart failure with preserved ejection fraction (HFPEF), ischemic cardiomyopathy, mixed etiology and other (for example, pericardial disease, adult congenital heart disease, arrhythmogenic right ventricular cardiomyopathy). The diagnosis of non-ischemic cardiomyopathies will be based upon the 2008 Canadian Cardiovascular Society Consensus conference guidelines [37].

#### Expected result

The routine CMR arm will have a significantly higher rate of infiltrative, inflammatory, hypertrophic, ischemic, mixed and other cardiomyopathies than the selective CMR group.

### Follow-up

Clinical outcomes will be collected by telephone follow-up, and/or by hospital chart and electronic health record review at three and twelve months and then yearly up to four years, following completion of baseline scans. Data will be recorded on standardized case report forms. Quality of life questionnaires (MLHFQ and EQ5D) will be administered at each follow-up.

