### Secondary outcome measures

(i) Treatment effects: at three months and one year, the treating physician will be asked to reassess the HF etiology. The presence of each HF medication class will be re-assessed in addition to the overall number of cardiac medications. The presence of advanced HF therapies will additionally be recorded at each follow-up visit including: implantable device, electrophysiologic study/ablation, cardiac surgery/transplantation, and disease specific therapies (for example, phlebotomy for hemochromatosis; steroids for sarcoidosis).

(ii) Clinical endpoints: Composite Clinical Endpoints (CCE that is, death, cardiovascular (CV) death, HF admission), left ventricular function, QoL, referral to HF clinic, costs and safety will be assessed at three months, then annually for a minimum of one year and a maximum of four years.

Resource utilization and costs: regression methods will be used to assess the incremental costs associated with the routine use of CMR.

(iii) Echo/CMR variability: anonymized copies of CMR and echo studies will be sent to a core lab for interpretation in approximately 10% of cases in order to assess reproducibility and quality assurance of the results. Appendix A.

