#### Analysis populations

For the purposes of data analysis, three study populations will be considered: Intent-to-treat (ITT) population, As-treated population and Per-protocol population. The ITT population will be used for the main analysis for all primary and secondary objectives, except for the safety analysis where the As-treated population will be used. As a secondary analysis, the analyses will be repeated for the As-treated and Per-protocol populations.

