#### Primary analysis

For the primary analysis, the definitive diagnosis of cardiomyopathy between routine CMR versus echo with selective CMR, diagnosis will be compared using chi-square techniques. Potential confounding variables of the relationship between the imaging strategies and the primary endpoint will be assessed. In particular, propensity scores based on patient factors (for example, in/outpatient, NYHA class, HF duration, diabetes, atrial fibrillation) and site factors (for example, time-to-imaging, time-to-therapy) will be used in the analysis if necessary to adjust for potential differences. A logistic regression model will be used to assess the occurrence of the endpoints between the imaging strategies (model will include a group indicator variable) adjusting for any pertinent baseline differences identified.

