#### Secondary outcomes

For the binary secondary outcomes, such as CCE, referral to HF clinic and HF therapies, chi-square tests will be used to compare the imaging strategies. Logistic regression analysis will be used for adjusting any pertinent baseline differences identified. For continuous secondary outcomes, such as LV function, MLHFQ and EQ5D, analysis of variance will be used to compare trends over time between the imaging strategies. Analysis of covariance will be used for adjusting any pertinent baseline differences identified. For assessing the reproducibility of echo/CMR results, reliability statistics, including intra-class correlations and kappas, will be calculated to compare CMR and echo studies with the core lab interpretations.

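### Follow-up is timed from scan completion, a post-randomisation point that falls later on average in the routine-CMR arm, and the text does not say whether earlier events count

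*Protocol article*

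**What the plan says.** - **Time origin.** The Follow-up section of the protocol article places collection of clinical outcomes "at three and twelve months and then yearly up to four years, following completion of baseline scans". The quality-of-life questionnaires are given at each of these contacts. Data come from telephone contact and/or review of charts and electronic records.
- **Order of tests.** The CMR section states: "Following all HF investigations (including echocardiography), study participants randomized to routine CMR as well as those requiring selective CMR will undergo a conventional scan".
- **Randomisation.** The text under Figure 1 states: "Consecutive patients will be enrolled at sites with CMR programs (defined as a minimum 200 cases/year) and randomized to routine CMR or selective CMR". It does not say whether randomisation comes before or after the echocardiogram.
- **Waiting time.** The same text says that "registry sites may become randomization sites if the experience and wait-time criteria are met". The Primary analysis section lists "site factors (for example, time-to-imaging, time-to-therapy" among possible adjustment variables. No length of wait is given in either place.
- **Clinical endpoints.** Under Secondary outcome measures, the CCE (death, cardiovascular death, HF admission), quality of life, costs and other endpoints "will be assessed at three months, then annually for a minimum of one year and a maximum of four years". No origin is restated there.
- **Analysis.** "For the binary secondary outcomes, such as CCE, referral to HF clinic and HF therapies, chi-square tests will be used to compare the imaging strategies". On populations: "The ITT population will be used for the main analysis for all primary and secondary objectives", with safety as the exception.
- **Costs.** The Economic evaluation section confines the analysis to the follow-up period held in the study database.

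**The concern.** In a randomised comparison the clock should start at the same point in both arms, and that point should not depend on allocation. Here it does. For most selective-arm patients the last baseline scan is the echocardiogram. For every routine-arm patient it is the CMR, which comes after everything else and after whatever wait the site has.

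Three things follow:

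- The 3-month, 12-month and yearly contacts fall later after randomisation in the routine arm.
- Events between randomisation and scan completion have no stated status.
- A patient who dies or withdraws before the CMR has no time zero, yet belongs in the intention-to-treat population.

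Patients enter with new or recently worsened HF, so the interval before the scan may be a period of raised risk. The CCE, treatment-change, quality-of-life and cost comparisons are at stake. The diagnostic yield, which is the primary outcome, is not.

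**Working it through.** **The plan's own figure.** The only stated number nearby is 252 per group, for a definitive diagnosis in 35% versus 50%, alpha 0.05, power 90% and 10% loss. With the two-sided pooled-variance z-test:

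n = [1.960 × √(2 × 0.425 × 0.575) + 1.282 × √(0.35 × 0.65 + 0.50 × 0.50)]² / 0.15² = 226.2, and 226.2 / 0.9 = 251.3, which rounds up to 252.

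The figure reproduces. It concerns the diagnosis and does not depend on where follow-up starts.

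**What must be assumed.** The article gives no scan delay, CCE rate or early hazard. The central illustration therefore assumes:

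- no true effect of the strategy;
- a CCE hazard of 0.6/year to day 90 and 0.2/year after;
- scans complete at day 7 in the selective arm and day 45 in the routine arm;
- 252 patients per arm.

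The risk over an interval is 1 − exp(−cumulative hazard).

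**Reading A: pre-scan events not counted (365 days from scan completion).**

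- Selective, days 7 to 372: (83 × 0.6 + 282 × 0.2)/365 = 0.2910, risk 25.2%.
- Routine, days 45 to 410: (45 × 0.6 + 320 × 0.2)/365 = 0.2493, risk 22.1%.
- Apparent risk ratio 0.87, favouring routine CMR.

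**Reading B: pre-scan events counted (randomisation to 365 days after scan completion).**

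- Selective, days 0 to 372: (90 × 0.6 + 282 × 0.2)/365 = 0.3025, risk 26.1%.
- Routine, days 0 to 410: (90 × 0.6 + 320 × 0.2)/365 = 0.3233, risk 27.6%.
- Apparent risk ratio 1.06, against routine CMR, because that arm is watched 38 days longer.

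**Anchored at randomisation (days 0 to 365, both arms).** (90 × 0.6 + 275 × 0.2)/365 = 0.2986, risk 25.8% in each arm, ratio 1.00.

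**First events before scan completion.** Routine: 252 × [1 − exp(−45 × 0.6/365)] = 18.0. Selective: 252 × [1 − exp(−7 × 0.6/365)] = 2.9.

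**Range.** The same formulas, with the selective arm at day 7 and a hazard of 0.2/year after day 90, give:

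| Early hazard/year | Routine scan day | A: selective vs routine (RR) | B: selective vs routine (RR) | Routine pre-scan first events of 252 |
|---|---|---|---|---|
| 0.2 (constant) | 45 | 18.1% vs 18.1% (1.00) | 18.4% vs 20.1% (1.09) | 6 |
| 0.4 | 28 | 21.8% vs 20.9% (0.96) | 22.4% vs 23.3% (1.04) | 8 |
| 0.6 | 45 | 25.2% vs 22.1% (0.87) | 26.1% vs 27.6% (1.06) | 18 |
| 0.9 | 60 | 30.2% vs 22.7% (0.75) | 31.4% vs 33.3% (1.06) | 35 |

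A separate grid for reading A assumed a 12-month risk of 10% to 30% and an early hazard over three months of 2 to 3 times the later one. It gave ratios of 0.89 to 0.97 for an extra delay of half a month to one month, and 0.68 to 0.89 for two to three months. At constant hazard the ratio was 1.00.

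**Costs.** No arithmetic applies. If the follow-up period starts once scans are done, restricting the cost analysis to it could, read literally, leave out pre-scan admissions and the CMR itself. Yet Secondary outcome measures sets out to estimate the incremental cost of routine CMR.

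**The case against.** The strongest reply is that the Follow-up section says when data are collected, not from when events count. No section excludes events before the scan. Chart and record review can look back, the main analysis is intention-to-treat, and a committee adjudicates each clinical event. All of this stands, and it rules out several stronger readings that a reader might infer:

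- **That early routine-arm deaths and admissions are excluded.** The text has no such rule.
- **That the bias necessarily favours routine CMR.** Reading B reverses it.
- **That this is immortal time.** That term means event-free time credited to a group. The possible problem here is early time left out, or an unequal window.
- **That the schedule contradicts intention-to-treat.** A visit schedule removes nobody. The difficulty is narrower: a patient who dies unscanned has no defined origin.

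It is also fair that some selective-arm patients have CMR, which narrows the gap, and that the wait-time criterion for randomising sites may keep delays short. The place of randomisation relative to echo is not stated, so day 7 is itself an assumption.

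One could add that the event origin may be set in a fuller protocol or analysis plan. That does not dispose of the point, because the article does state an origin for contacts and that origin depends on the arm. Counting pre-scan events does not repair it either: a chi-square on a binary CCE makes no allowance for unequal observation time.

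**Conclusion.** The point holds in a limited form. The stated origin for follow-up contacts lies after randomisation, is later on average in the routine arm, and is undefined for a patient never scanned. Whether pre-scan events count is not stated, and under either reading the arms are observed over different windows measured from randomisation.

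In the central illustration the spurious one-year CCE difference is about 3 points in favour of routine CMR, or 1.5 points against it. These figures rest wholly on assumed delays and hazards. If pre-scan events are not counted, there is no bias in the rate at constant hazard and only a small one for delays of a month or less. The real size and direction cannot be derived from the article.

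Only secondary outcomes are affected, so this ranks below must-fix. It still merits action, because the remedy is specific and cheap.

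**What to change.** - Make the date of randomisation time zero in both arms for CCE, treatment, quality-of-life and cost outcomes.
- Schedule the 3-month, 12-month and yearly contacts from that date.
- Count all events and costs from randomisation, including the CMR itself, and including patients who die, withdraw or are never scanned.
- Word the cost window in the Economic evaluation section to match.

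The cost is a change of wording in the protocol and case report forms. For patients already enrolled, events and admissions before the scan can be sought through the chart and electronic record review already planned. Quality-of-life contacts already made on the scan-based clock cannot be moved, so their actual time since randomisation should be recorded and used in the analysis. The sample size does not change.
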